## 12.3 Statistical and Data Management Coordinating Centers

All data collection and transfers to the Data Manager will be conducted by MUHAS. The study Data Manager in Delhi, India, [name], will provide oversight and advise both sites in local data management. [name] has been responsible for data collection design, consolidation, and quality assurance for a number of large clinical trials in Tanzania. UNC will be primarily responsible for statistical analysis, including oversight of analysis conducted at MUHAS.

## 12.4 Study Site Monitoring

### 12.4.1 Intervention

Day-to-day monitoring, supervision, and support of the microfinance and health leadership intervention components will be led by the intervention coordinator, who will periodically observe microfinance repayment sessions and meet with Camp Health Leaders to discuss progress in implementing health promotion training within the camps. The intervention coordinator will supervise loan officers and solicit periodic reports on progress of the microfinance component in the camps.

### 12.4.2 Data Management

Study PIs will generate a list of criteria to be used for on-site data management quality control and monitoring. Study staff responsible for collecting and transferring data to the data manager will be in regular contact with the data manager for data monitoring and review.

### 12.4.3 Documentation

Regular monitoring of study documentation will be performed by UNC and MUHAS to ensure proper recording, reporting, and storage of all study documentation.

## 12.5 Protocol Compliance

This study will be conducted in full compliance with the protocol. Amendments to the protocol will be reviewed and validated by study staff at both UNC and MUHAS. Protocol amendments requiring IRB approval will be submitted to relevant IRBs by the study sites’ Principal Investigators, and approval obtained prior to implementing the amendment.

## 12.6 Minimizing Risks to Staff

All staff members obtaining and handling blood samples for the study will have received training in proper procedures to minimize risks associated with occupational exposure to blood-borne pathogens. All staff will follow standard safety procedures and will have appropriate supplies available to minimize such risks. Protocols will be in place to provide postexposure prophylaxis (PEP) for any study-related occupational exposures to HIV.

## 12.7 Investigator Records

All project primary source documents will be maintained in a secure location for a period of five years after documents are considered complete and utilized. Primary source documents will be stored at field office locations in locked cabinets. Primary source documents will be made available to authorized personnel upon request.

## 12.8 Policy on Data Sharing

Project data sets will be housed at both UNC and MUHAS, and will be password protected. All Principal Investigators (both U.S. and host country) will be given access to the cleaned data sets. Individuals outside the primary study team are required to submit a data acquisition form that outlines desired variables. To ensure confidentiality, data dispersed will be blinded of any identifying participant information.

## 12.9 Dissemination of Study Results

Timely and rigorous analysis and dissemination of study data is a major responsibility the project has to the study participants and the research field. We recognize that there are many important means of dissemination of study results, including publications, presentations at meetings, and in-country dissemination activities.

The project PIs must give study staff permission to proceed with dissemination submissions and will provide manuscript review for publications with the goal of ensuring that all manuscripts, publications, and other products generated from the study accurately represent its design, implementation, and analysis. Both manuscripts and abstracts will require review by the PIs prior to submission to the journal/conference.

The PIs of this study will develop a list of potential publications for the study and will have first selection on publication development. Other study group members will be given the opportunity to become involved or lead in proposed analyses and dissemination activities. Study members can also propose additional analyses and publications not generated by study PIs. If approved by the study PIs, the study staff will have 6 months to produce a draft to the study team. If no product has been submitted by the end of this time period, the authors forfeit their claim to the proposed analysis, and the analysis will be assigned to new authors.

Proper recognition will be given to all study group members participating sufficiently in the publication process. Authorship of all study manuscripts will reflect standards of scientific paper authorship, including that all authors have made an intellectual contribution to the design, implementation, interpretation, and/or analysis of the study, and have participated in the study and the preparation of the manuscript sufficiently to assume public responsibility for the content of the manuscript.

All peer-reviewed manuscripts and presentations must acknowledge the funding source for this project with the following statement,

*“This research was sponsored by the U.S. National Institute of Mental Health (5R01MH098690).” In addition, authors of manuscripts may choose to acknowledge key staff members and others who were involved in the research but do not meet the criteria for authorship.*

Tool Revision History:

| ****Version Number**** | Version Date | Summary of Revisions Made: |
| --- | --- | --- |
| 1.0 | 11Feb2013 | Original version with Tool Summary Sheet |
| 2.0 | 23Sep2015 | Updated intervention implementation text |

**APPENDIX A**

Vijana Vijiweni II/YOSEFO: Entrepreneurship Training Schedule

| DAY | TIME | TOPIC |
| --- | --- | --- |
| Monday | 8:30 a.m. – 9:00 a.m. | Registration |
|  | 9:00 a.m. – 10:30 a.m. | Introduction and Training Overview |
|  | 10:30 a.m. – 11:00 a.m. | Tea |
|  | 11:00 a.m. – 1:00 p.m. | Entrepreneurship |
|  | 1:00 p.m. – 2:00 p.m. | Lunch |
|  | 2:00 p.m. – 3:30 p.m. | Entrepreneurship (Continued) |
|  | | |
| Tuesday | 8:30 a.m. – 9:00 a.m. | Review of Day 1 |
|  | 9:00 a.m. – 10:30 a.m. | Skills for Entrepreneurship |
|  | 10:30 a.m. – 11:00 a.m. | Tea |
|  | 11:00 a.m. – 1:00 p.m. | Business Environment |
|  | 1:00 p.m. – 2:00 p.m. | Lunch |
|  | 2:00 p.m. – 3:30 p.m. | Marketing and Sales Techniques |
|  | | |
| Wednesday | 8:30 a.m. – 9:00 a.m. | Review of Day 2 |
|  | 9:00 a.m. – 10:30 a.m. | How to Start a Business |
|  | 10:30 a.m. – 11:00 a.m. | Tea |
|  | 11:00 a.m. – 1:00 p.m. | Ways to Expand a Business |
|  | 1:00 p.m. – 2:00 p.m. | Lunch |
|  | 2:00 p.m. – 3:30 p.m. | Ways to Expand a Business (Continued) |
|  | | |
| Thursday | 8:30 a.m. – 9:00 a.m. | Review of Day 3 |
|  | 9:00 a.m. – 10:30 a.m. | Regulation of Credit |
|  | 10:30 a.m. – 11:00 a.m. | Tea |
|  | 11:00 a.m. – 1:00 p.m. | Procedures for Loan Repayment |
|  | 1:00 p.m. – 2:00 p.m. | Lunch |
|  | 1:00 p.m. – 3:30 p.m. | Procedures for Loan Repayment (Continued) |
|  |  |  |
| Friday | 8:30 a.m. – 9:00 a.m. | Review of Day 4 |
|  | 9:00 a.m. – 10:30 a.m. | How to Estimate Cost |
|  | 10:30 a.m. – 11:00 a.m. | Tea |
|  | 11:00 a.m. – 1:00 p.m. | Pricing |
|  | 1:00 p.m. – 2:00 p.m. | Lunch |
|  | 1:00 p.m. – 3:30 p.m. | Pricing (Continued) |
|  | | |
|  | 3:00 p.m. – 3:30 p.m. | Group Formation |

**APPENDIX B**

First Loan Application Fees and Repayment Plan

**
[figure not shown]
**

**APPENDIX C**

Camp Health Leader Training Schedule

| **Time** | **Activities** | | | **Responsible Personal** | | |
| --- | --- | --- | --- | --- | --- | --- |
| **Day 1: Introduction, Leadership, Introduction to HIV/AIDS** | | | | | | |
| 8:00 – 8:15 | | Registration  [Pre test] | | [name] | | |
| 8:15 – 9:00 | | Welcome, Introduction & Overview of the Program | | [name] | | |
| 9:00 -10:00 | | The AIDS Epidemic in the World and Your Community | | [name] | | |
| 10:00 -10:30 | | Tea Break | | ALL | | |
| 10:30-12:30 | | HIV Myths and Facts | | [name] | | |
| 12:30-13:00 | | Who is a Leader? | | [name] | | |
| 13:00 – 14:00 | | Lunch Break | | ALL | | |
| 14:00 – 14:30 | | What are we asking you as a CHL? | | [name] | | |
| 14:30 – 15:30 | | Correcting HIV/STI Myths & Communication Facts | | [name] | | |
| 15:30 – 16:00 | | Visiting Health Facilities  Wrap-up & Evaluation | | [name] | | |
| **Day 2: Gender Based Violence & Alcohol** | | | | | | |
| 8:00-8:30 | | Review | | | [name] | |
| 8:30-9:30 | | Power, Control & Violence (My Planet) | | | [name] | |
| 9:30-10:15 | | GBV Activity (in Her Shoes) | | | [name] | |
| 10:15-10:45 | | Tea Break | | | ALL | |
| 10:45-11:45 | | Masculinity | | | [name] | |
| 11:45-13:00 | | Consent Vs Coercion: Attitudes Towards Rape | | | [name] | |
| 13:00-14:00 | | Lunch Break | | | ALL | |
| 14:00-15:00 | | Alcohol and HIV Risk Behaviour | | | [name] | |
| 15:00-15:45 | | Values around Gender and Alcohol use | | | [name] | |
| 15:45-16:00 | | Wrap-up & Evaluation of Day 2 | | | [name] | |
| **Day 3: So what? Learning about Skills: Condom Use, Problem Solving, and Crafting Messaging** | | | | | | |
| 8:00-8:30 | | | Review | | | [name] |
| 8:30-10:00 | | | Introduction on STI, Condom Demonstration and Condom Myths  [Assign HW # 1: Visit HIV/STI facilities  Assign # 2 [Buy Condoms] | | | [name] |
| 10:00-10:30 | | | Tea Break | | | ALL |
| 10:30-12:00 | | | Problem Solving Triggers Activity with Scenarios | | | [name] |
| 12:00-13:00 | | | Planning for the Future and Why it matters | | | [name] |
| 13:00-14:00 | | | Lunch Break | | | ALL |
| 14:00-15:00 | | | Characteristics of Effective HIV/STI Prev Messages | | | [name] |
| 15:00-15:45 | | | Create Messages using “I” Statements | | | [name] |
| 15:45-16:00 | | | Wrap-up & Evaluation of Day 3 | | | [name] |
| **Day 4: Initiating Conversation Using Effect Prevention Messages** | | | | | | |
| 8:00-8:30 | | | Review | | | [name] |
| 8:30-10:00 | | | Practice Delivering Effective Prevention Messages  Group Activity-Formulating Prevention Messages, Presentation and Voting | | | [name] |
| 10:00-10:30 | | | Tea Break | | | ALL |
| 10:30-11:30 | | | Countering Negative Views About Sex | | | [name] |
| 11:30-13:00 | | | Communication and Interpersonal Skills Training | | | [name] |
| 13:00-14:00 | | | Lunch Break | | | ALL |
| 14:00-15:45 | | | Role play initiating Conversation  Assign # 3 [practice Initiating Conversation] | | | [name] |
| 15:45-16:00 | | | Wrap-up & Evaluation of Day 4 | | | [name] |
| **Day 5: Helping Others Overcome Barriers to safer Behavior** | | | | | | |
| 8:00-8:30 | | | Review | | | [name] |
| 8:30 -10:000 | | | Identify & Addressing Barriers to Practicing Safe Sex | | | [name] |
| 10:00-10:30 | | | Tea Break | | | ALL |
| 10:30-12:00 | | | CHL Role play Practicing of Giving Advice | | | [name]/[name] |
| 12:00-13:00 | | | Planning & Documenting Effective Conversations | | | [name]/[name] |
| 13:00-14:00 | | | Lunch Break | | | ALL |
| 14:00-14:15 | | | Referral Information | | | [name] |
| 14:15-15:00 | | | Next Steps and Evaluation & Conclusion  [Written Evaluation of Entire Training] | | | ALL |
| 15:00-15:30 | | | Graduation and Certificates Given  [Condom Distribution] | | | ALL |

**­APPENDIX D**

**Health Knowledge and Behavior Survey**

**Microfinance and Health Study**

Table of Contents

Section 0: Confirming Eligibility 2

Section 1: Background 3

Section 2: State of Hope Scale 5

Section 3: Future Orientation 5

Section 4: Social Cohesion 7

Section 5: Collective Efficacy 8

Section 6: Emotional Distress (HSCL 25) 8

Section 7: Gender Equitable Men’s Scale 10

Section 8: Conflict Tactics Scale 12

Section 9: HIV Stigma 19

Section 10: Alcohol and Drug Use 19

Section 11: Social Support 20

Section 12: Social Network 22

Section 13: Attitudes towards HIV Risk Behaviors and Intimate Partner Violence 26

Section 14: Sexual Relationships and Risk Behaviors 27

Section 15. Sexual Network 29

Section 16: Work and Expenditures 35

Section 17: Closing 39

Section 0: Confirming Eligibility

Interviewer:

**→ You have been chosen to participate in a study. I would like to tell you more about the study so that you can decide if you would like to participate. Before we begin, I would like to ask you a few brief questions.**

| **No.** | **Questions and Filters** | **Coding Categories** | **Codes** | **Skip to:** | **VARIABLE** |
| --- | --- | --- | --- | --- | --- |
| Q001 | [DO NOT READ OUTLOUD]  Is this participant able to provide informed consent (i.e. the person does not have a permanent physical disability (e.g. deafness) or mental disability which prevents them from providing consent)? | NO  YES | 0  1 | **END** | ELIG1 |
| Q002 | What is your date of birth?  Note: If the participant does not know his/her date of birth, please enter 1900 for the year. | (Day)___ ___ / (Mo.)___ ___ (Year)___ ___ ___ ___ |  |  | ELIG2 |
| Q003 | How old are you? | __ __ Years |  |  | ELIG3 |
| Q004 | [DO NOT READ OUTLOUD]  Is the participant older than 15 years old?  Note: If the respondent was born after today’s date in 1998, or later (Younger than age 15), then the participant is not eligible. | NO  YES | 0  1 | **END** | ELIG4 |
| Q005 | How long have you been a member of camp X?  Note: Look at the Participant Contact Form for the name of the camp | __ __ YEARS  __ __ MONTHS |  | **If Years is ≥ 2, then enter 0 for Months** | ELIG5 |
| Q006 | [DO NOT READ OUTLOUD]  Has the participant been a member of camp X for at least 3 months? | NO  YES | 0  1 | **END** | ELIG6 |
| Q007 | How often would you say you come to camp X? | EVERY DAY  SEVERAL TIMES A WEEK  ONE TIME PER WEEK  COUPLE TIMES A MONTH  ONE TIME PER MONTH  LESS THAN ONCE A MONTH | 1  2  3  4  5  6 | **END**  **END**  **END** | ELIG7 |
| Q008 | Are you a member of any other camps? | NO  YES | 0  1 | **Q012** | ELIG8 |
| Q009 | What are the names of these other camps?  *Note: If participant is a member of more than 2 other camps, separate these camp names with a comma.* |  |  |  | ELIG9 |
| Q010 | [DO NOT READ OUTLOUD]  By looking at the list of 60 study camps, determine whether participant is a member of another study camp. Is the participant a member of another study camp? | NO  YES | 0  1 | **Q012** | ELIG10 |
| Q011 | I see that you are also a member of camp X. Which of these camps would you consider to be your PRIMARY CAMP? By primary camp, I mean you spend more time in this camp than any other camp. | This Camp  Other Camp |  | **END** | ELIG11 |
| Q012 | Have you answered these types of questions and have you previously provided a sample of your blood and urine to our study staff? | NO  YES | 0  1 | **END** | ELIG12 |
| Q013 | Do you plan to live in Dar es Salaam for the next 30 months? | NO  YES | 0  1 | **END** | ELIG13 |
| Q014 | Are you willing to provide a phone number and contact information for two family members or close friends so that study staff can contact you in the future? | NO  YES | 0  1 | **END** | ELIG14 |

*Interviewer:*

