## 3.3 Study Duration and Endpoints

The intervention will be implemented for two years, and the total duration of the trial will be 5 years. **The primary endpoints** are sexually transmitted infections including Neisseria gonorrhea (NG), Trichomonas vaginalis (TV), Chlamydia trachomatis (CT), and perpetration of physical or sexual violence against a sexual partner. A random sample of 50% of participating men will be flagged for an STI test at baseline to assess relative prevalence, and all men will be tested at endline. A test of relative prevalence at baseline will aid in establishing equivalency in the two arms; any lack of equivalency then will be controlled for appropriately at endline. All participants will complete a behavioral assessment at baseline, 12 months and 30 months to assess secondary objectives. **Secondary endpoints** are HIV risk and protective behaviors including: gender equity, alcohol and drug use, sexual relations and risk behavior, uptake of HIV counseling and testing; unprotected sexual intercourse; consistent condom use; delay of sexual debut; number of sexual partners, and sexual concurrency. **Key mediators** are hope, future orientation, social cohesion, collective efficacy, emotional distress, sexual networks, social support and social influence.

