## 6.4 Baseline STI Assessment

Urine and blood specimens for diagnosis of STIs (NG, TV, CT) and HIV will be requested from a sample of half of sexually active men at baseline. Baseline testing is employed to compare base prevalence in the two conditions.

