## 10.8 Incentives for Participation

Participants will be reimbursed TSH 10,000 (~$6.25) for the transportation costs incurred to travel to the interview site and for the time that they spent in transit to and during the interviews. This includes participation in the baseline behavioral and biological assessment, and the 12 and 30 month follow-ups. Health Leaders nominated from camps will receive TSH 10,000 (~$6.25) for each day present of the 5-day training. Likewise, all camp members eligible for the microfinance component will receive TSH 10,000 (~$6.25) for each day present during the business and entrepreneurship training.

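### The repeat-participation item behind the primary-camp screen (Q012) lets through men who were interviewed but never sampled

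*Protocol*

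**What the plan says.** Appendix D, Section 0 has two barriers against enrolling the same man twice.

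- **Primary-camp screen (Q008-Q011).** Everyone is asked "Are you a member of any other camps". Camps that he names are compared with the study list: "By looking at the list of 60 study camps, determine whether participant is a member of another study camp". If one of them is a study camp, he is asked "Which of these camps would you consider to be your PRIMARY CAMP". The skip column shows END at this item. The extracted table does not tie END to an answer, but the other camp is the only sensible one.
- **Repeat-participation item (Q012).** "Have you answered these types of questions and have you previously provided a sample of your blood and urine to our study staff". Again the only sensible reading is that YES ends the interview.

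The protocol describes baseline sampling in two ways. Section 3.3 says "A random sample of 50% of participating men will be flagged for an STI test at baseline". Section 6.4 says that specimens "will be requested from a sample of half of sexually active men at baseline". Under section 10.2, men not selected are offered a symptom-based assessment only, so they give no specimen.

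Section 4.3 puts name, birthdate and phone numbers on each camp roster. It states no comparison between rosters.

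**The concern.** Q012 matters only for a man who has got past Q008-Q011, and for him it is the last check. Its YES requires both a prior interview and a prior specimen. A man already interviewed through another study camp but not chosen for sampling can truthfully answer NO and go on to a second enrolment.

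He would then hold two participant numbers in two camps. If both camps are in the same arm, one man counts as two observations in different clusters, which slightly overstates precision. If they are in opposite arms, his outcomes enter both sides of the comparison, and his control record belongs to someone with access to the intervention. That would pull the estimate towards no difference.

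Each attendance carries a payment ("Participants will be reimbursed TSH 10,000 (~$6.25) for the transportation costs", section 10.8), so a man has some reason to attend twice and little reason to volunteer that he has done so.

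**Working it through.** No figure in the protocol's sample-size section depends on this point, so there is no stated result to reproduce. The check traces the skip pattern and then works out a pass rate.

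**Routes to Q012 for a man already interviewed through another study camp**

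1. He answers NO at Q008. He skips to Q012, and the comparison with the list of 60 camps at Q010 is never made.
2. He declares the other camp but says at each interview that the present camp is his primary one. Q011 does not end either interview.
3. He declares both camps and names the same primary camp each time. The interview at the other camp ends at Q011 and he is enrolled once, whether or not he was sampled.

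Only routes 1 and 2 reach Q012.

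**Share of previously interviewed men whom a literal Q012 lets through**

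Inputs:
- share sampled, section 3.3: 0.5 of participating men;
- share sampled, section 6.4: 0.5 of sexually active men;
- sexually active share, from the average camp in section 9.1.1: 36.2/52 = 0.696.

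Pass rate = 1 - share sampled.

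- Under section 3.3: 1 - 0.5 = 0.50.
- Under section 6.4: 1 - 0.5 × 0.696 = 1 - 0.348 = 0.652, about 65%.

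Refusal of specimens would raise both figures. Both assume that repeat attenders were sampled at the same rate as other men, and that they answer the item as worded.

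**Other controls stated in the protocol**

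- Q010 compares camp names, not people.
- The paper and tablet records in section 6.10 are reconciled by participant number, which would not reveal one man with two numbers.
- Section 6.3 splits interviewers between four wards, so recognition by an interviewer cannot be relied on.
- Section 4.1.4 gives selected camps from the same geographic group the same condition. This rules out an opposite-arm duplicate within a group, but not between groups.

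**The case against.** The strongest reply is that Q008-Q011 already deal with the man on two rosters. That stands. A reader might infer that the screener stops only men who were both interviewed and sampled, or that any unsampled man on two rosters can be enrolled twice. Neither follows, because a man who answers openly and consistently is enrolled once.

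A reader might also want a count of duplicates, with about half of them split across arms. The documents support neither. They give no rate of repeat attendance, and the 50% and 65% apply only to men who have already passed the first barrier. Shared membership may well be commonest between neighbouring camps, which section 4.1.4 keeps in one arm. Nor do all duplicates bias the result towards no difference: same-arm duplicates affect precision, and only opposite-arm ones dilute the contrast.

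Further replies have some force. A man who hides a membership for the payment could also deny a prior interview, so rewording helps mainly with men who answer literally or name each camp as primary in turn. The pre-test of survey items in section 6.2 might expose the compound wording. Q111-Q113 record other camps visited, so overlap can be examined later. Section 7.6.2 ties loan eligibility to completing the baseline survey, which limits loan access for a man turned away at an intervention camp. It does not limit it for a man who completes the survey through both camps.

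The absence of a roster match from section 4.3 is not an error in itself. What remains is a stated check that, as worded, fails for half or more of the men it is there to catch.

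**Conclusion.** The point holds as a minor fault of the instrument. Read literally, Q012 passes about 50% to 65% of previously interviewed men who reach it, depending on which description of baseline sampling applies, and more if specimens are refused. Double enrolment is then possible for a man who does not declare his second study camp, or who calls each camp primary in turn. It crosses arms only if the two camps lie in different geographic groups and are assigned differently.

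The number of such men cannot be worked out from the protocol and is probably low, so no material effect on the trial's result has been shown. The conclusion rests on the literal wording, on YES being the answer that ends the interview, and, for the 65%, on the planning figure of 36.2 sexually active men in 52.

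**What to change.** - **Split Q012 at baseline.** Ask first whether the man has already completed this study's interview through any camp, and end on YES whatever his specimen history. Ask about a prior specimen separately if it is wanted. Limit the rule to baseline, because section 8.2.3 uses the same survey form at 12 and 30 months, when every returning participant has been interviewed before.
- **Match the 60 rosters** on name, birthdate and phone number. Keep one record per matched man, in his primary camp, by a rule written before outcomes are seen. This also covers men who would not disclose a second camp.

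The first change costs one questionnaire item. The second uses data already collected and existing staff. If baseline is closed, the match can still be run retrospectively under the same rule.
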